## Abstract

**Background:**

A frequent and increasing indication for liver transplantation (LT) is hepatocellular carcinoma (HCC). However, despite strict selection criteria, HCC recurrence after LT occurs in a relevant proportion of patients and is associated with an unfavorable prognosis. Hypothermic oxygenated perfusion (HOPE) is a novel machine liver perfusion approach to optimize liver grafts before implantation and has been suggested to decrease graft inflammation with potential anti-cancer effects.

**Methods:**

HOPE4Cancer is an international, multicentric, parallel group, randomized controlled trial comparing HOPE performed after initial cold storage (intervention) with conventional cold storage alone (control) in a 1:1 allocation ratio. Adult recipients with proven HCC will be included for transplantation of a DBD (donation after brain death) Liver graft. The minimum perfusion duration is defined at 2 h and perfusion is generally continued until the recipient hepatectomy is completed. The conventional cold storage at 4 °C will be performed with a precooled preservation solution according to the local standard of care. The primary endpoint is defined as post-transplant HCC recurrence-free survival, i.e., the time interval a patient is alive without HCC recurrence after transplantation. Secondary endpoints are the single components of the events considered for the primary outcome (i.e., HCC recurrence, HCC-related death, death from any other causes than HCC), circulating tumor DNA, high-mobility-group-protein B1 in the blood, the Rejection Activity index, and the number of liver-related complications experienced by the patient.

**Discussion:**

HOPE4Cancer investigates if cold storage plus end-ischemically applied HOPE in DBD LT is superior to conventional cold storage of liver grafts in terms of post-transplant HCC recurrence-free survival. The results will indicate for the first time whether ex situ HOPE before transplant has an anti-cancer potential compared to transplantation of un-perfused livers.

**Trial registration:**

ClinicalTrials.gov NCT06717919. Registered on December 5, 2024.

## Introduction

### Background and rationale {6a}

Hepatocellular carcinoma (HCC) is the most common primary liver cancer, and liver transplantation for early HCC stages is the treatment of choice [1, 2]. Liver transplant results in excellent outcomes with overall 5-year survival rates of 70% [3]. However, HCC recurrence may occur after LT and is reported in up to 15% of cases, associated with poor outcome [4, 5]. The mechanisms for HCC recurrence after hepatectomy and liver transplantation (LT) are not yet fully understood. Several factors, including tumor seeding, unrecognized residual micro-lesions in lymph nodes, active hepatitis, increased liver regeneration, and immunosuppressive treatment, may promote cancer growth or recurrence [6]. In addition, ischemia reperfusion injury has been recognized as an important initial driver of microvascular dysfunction with subsequent tissue hypoxia and ongoing inflammation, which promotes tumor cell reseeding and growth [6]. Accordingly, in a cascade-like mechanism, ischemia reperfusion injury (IRI) leads to hepatic sinusoidal injury, which causes dysregulation of the hepatic microcirculatory barrier and activates cell signaling related to invasion and migration [7]. Hypoxia triggers gene upregulation and release of cytokines, involved in angiogenesis, cellular proliferation, growth, and adhesion. In the absence of oxygen, hypoxia-inducible transcription factor 1 (HIF-1a) binds to hypoxia-response elements, thereby upregulating the hypoxia-response gene expression, including vascular endothelial growth factor [8, 9]. Inflammatory mediators, including reactive oxygen species (ROS) and numerous cytokines (TNFα, IL-1, IL-6, IFN-y) released from various immune cells, induce epigenetic alterations in premalignant lesions and silence tumor suppressor genes [10, 11]. It is currently hypothesized that a key link between inflammation and cancer recurrence may originate from mitochondria. An early mitochondrial protection may therefore be decisive for decreasing tissue inflammation and subsequent tumor cell seeding (Fig. 1).

**Fig. 1 Fig1:**
[figure not shown]
Postulated protective mechanism of machine liver perfusion against cancer recurrence. Modified from Maspero et al., JHPE 2023 [38]

During the past 10 years, organ machine perfusion has regained clinical interest due to advantages compared to cold static storage. For example, machine liver perfusion reduces post-transplant complications and increases graft survival by improving early allograft function [12]. Hypothermic oxygenated perfusion (HOPE) has recently gained popularity due to its simplicity besides clinical efficacy. First, it is performed at the recipient center after organ transport, i.e., cold storage, and therefore does not change current practice in organ procurement. Secondly, it reduces significantly IRI by mitochondrial reprogramming [13–15]. Thirdly, it is particularly beneficial in extended criteria donor livers, such as steatotic livers and livers donated after circulatory death (DCD). Mechanistically, HOPE leads to full metabolization of accumulated succinate and NADH, together with replenished cellular ATP pools and improved function of mitochondrial complexes I–IV. This leads consecutively to decreased inflammation signals during implantation and may therefore potentially reduce also the risk of HCC recurrence [14, 16, 17]. Accordingly, a retrospective study reported a significant reduction of tumor recurrence rate from 25.7% in un-perfused donation after brain death (DBD) Livers compared to only 5.7% in HOPE-treated DCD organ recipients [14].

This study therefore aims at showing that post-transplant HCC recurrence-free survival (RFS) is improved by end-ischemically applied HOPE before transplantation, compared to standard conventional cold storage in patients who undergo liver transplantation for HCC.

### Objectives {7}

The overall objective of this trial is to investigate the anti-tumor effects of HOPE before liver transplantation in patients with HCC. The primary objective is to show that HCC recurrence-free survival is improved with HOPE compared to conventional cold storage alone in patients with liver transplantation for HCC.

### Trial design {8}

HOPE4Cancer is an international, multicentric, parallel group, superiority randomized controlled trial (RCT) comparing HOPE to conventional cold storage. Patients will be allocated in a 1:1 ratio.

## Methods: participants, interventions and outcomes

### Study setting {9}

The trial will be conducted in approximately 34 academic tertiary referral centers that have implemented HOPE before the start of the trial. Centers are in Switzerland, other European countries, and the USA (Fig. 2).

**Fig. 2 Fig2:**
[figure not shown]
Study sites

### Eligibility criteria {10}

The following are inclusion criteria for patients:Adult recipients (> 18 years old)Listed for liver transplantationDocumented HCC (LIRADS-5 lesion in MRI or CT of the liver or biopsy proven) within up to seven criteria, i.e., HCC with seven as the sum of the diameter of the largest tumor (in cm) and the number of tumors at the timepoint of liver transplantation. This includes also patients beyond the up to seven criteria after successful downsizing of the HCC.Written informed consent for the trial

The following exclusion criteria will be applied:DCD liver graftsCombined liver transplantsPartial liver transplantsCombined or mixed hepatocellular cholangiocarcinoma or pure cholangiocarcinoma or other malignancies in histopathology of the liver explantSystemic antitumoral medical treatment with checkpoint inhibitors or multikinase inhibitorsPost-transplant treatment with mTOR inhibitorsAcute and unexpected medical contraindicationPregnancyCold storage time of > 10 h (in both study arms)

### Who will take informed consent? {26a}

All participants will be provided a participant information sheet and a consent form describing the study and providing sufficient information for participants to make an informed decision about their participation in the study. The time frame given is at least 7 days. The formal consent of a participant, using the approved consent form, must be obtained before the participant is submitted to any study procedure. The investigators or a designee will take consent in the outpatient clinic.

### Additional consent provisions for collection and use of participant data and biological specimens {26b}

Participants will be asked in the consent form if they agree to the use of their data should they choose to withdraw from the trial. Participants will also be asked for permission for the research team to share relevant data with people from the universities and regulatory authorities taking part in the research. In addition, all participants will be asked whether they agree to the further use of health-related data or not.

## Interventions

### Explanation for the choice of comparators {6b}

Conventional cold storage after organ procurement has been the standard of care before the implementation of machine perfusion for liver grafts and is currently still the most commonly used method. It involves storage of the organ on ice. Every transplant center is familiar with the procedure and no additional training or material is required for the storage procedure in the control arm.

### Intervention description {11a}

All study centers will use either a VitaSmart®, Liver Assist®, or Perlife® device for machine liver perfusion (Fig. 3), with a pressure-controlled hypothermic oxygenated liver perfusion through the portal vein (HOPE) or through the portal vein and the hepatic artery (DHOPE). The rationale to choose VitaSmart® and Liver Assist® is based on their CE sign and the clinical experience during recent and ongoing RCTs [18–20] (NCT05045794). Perlife® also has a CE sign and is used currently in another RCT (NCT04644744). There are no RCTs comparing the effectivity of HOPE vs. DHOPE. However, recent cohort and experimental data show no differences between HOPE and DHOPE in terms of perfusion quality and also in terms of outcome [18, 21–23]. The oxygenation process of the perfusate is similar, as the same oxygenators are used. The perfusion flow in both procedures is pressure controlled. For the sake of simplicity, we therefore refer to HOPE/DHOPE as HOPE throughout the manuscript. The targeting pressure is 3–5 mmHg and the perfusate temperature is between 8 and 12 °C. The perfusate consists of 3L recirculating Belzer MPS® (Bridge to Life Ltd.) with active oxygenation (70–110 kPa). The minimum perfusion duration is defined as 2 h, while perfusion is generally continued until the recipient hepatectomy is completed, i.e., if the recipient hepatectomy takes longer, perfusion is extended. The absolute upper Limit for HOPE is 24 h according to recent publications [24, 25]. The perfusion device is routinely used in all participating centers. All machines used are certified for human use and controlled by transplant surgeons. Cooling of the perfusate is managed by a heat exchanger (Liver assist®) or ice (VitaSmart®); the perfusion flow is adjusted to 150–250 ml/min under pressure control (< 5 mm Hg). Commercially available, CE-certified and approved Belzer MPS solution will be used (Belzer MPS-UW-Machine perfusion solution, Bridge to Life®) as perfusate for machine perfusion (according to clinical routine).

**Fig. 3 Fig3:**
[figure not shown]
Machine perfusion technique and devices

### Criteria for discontinuing or modifying allocated interventions {11b}

If there are safety concerns or withdrawal of informed consent, patients are withdrawn from the study.

### Strategies to improve adherence to interventions {11c}

Minimal deviation from the protocol is expected due to the experience of the centers with both the intervention and the control procedures which are both part of the clinical routine in all centers. Nevertheless, cold storage time, the used preservation solution, the machine perfusion type, time, and oxygenation will be recorded and assessed to identify non-adherence.

### Relevant concomitant care permitted or prohibited during the trial {11d}

All concomitant care or interventions needed after transplantation are permitted, except that post-transplant mTOR inhibitors are prohibited.

### Provisions for post-trial care {30}

The post-transplant imaging for the HCC surveillance will be compensated. Otherwise, there is no additional study-related procedure and no deviation from the usual care after LT.

### Outcomes {12}

The primary outcome is post-transplant HCC recurrence-free survival, i.e., the time interval until either tumor recurrence is observed or the patient dies from any cause. HCC recurrence is assessed by computed tomography (CT) at 6, 12, 18, and 24 months (and every 6 months afterwards, if appropriate, until the end of the study), which will be checked for intrahepatic and extrahepatic masses according to the LiRADS classification. At least 24 months of follow-up duration for every patient is required. HCC recurrence is clinically highly relevant as only limited treatment options are available after liver transplantation. This time-to-event measurement will be aggregated as a hazard rate.

Secondary outcomes are:Single components of the events considered for the primary outcome, i.e., HCC recurrence (while alive), HCC-related death, and death from any other causes than HCC. As the primary outcome, each component will be analyzed as time to event (up to a minimum of 24 months) and aggregated as hazard rate.Circulating tumor DNA in blood (before transplantation, at discharge, and at 6 months after transplantation)High-mobility-group-protein-B1 (HMGB-1) in blood (at the time of transplantation and 1 week after transplantation)Rejection Activity index (RAI) in liver histology (biopsy) performed at 6 months post-transplantationNumber of Liver-related complications experienced by the patient within 2 years

Other outcomes of interest are:Spatial transcriptomics of T cells (CD4 +, CD8 +) and monocytes (CD14 +) in liver biopsies at the end of implantationLaboratory parameters AST/ALT/bilirubin, AP, INR, measured daily during the first week after transplantationEarly allograft dysfunction (EAD) based on laboratory parameters measured over week 1 after transplantationParameters assessed in the liver explant of the patient (phenotyping of tumor infiltrating and tumor stroma immune cells in liver explants, RNA sequencing, metabolomics and spatial pathology in tumor and tumor stroma in liver explants)

### Participant timeline {13}

The participant timeline is shown in Table 1.

**Table 1 Tab1:** Schedule of enrollment, intervention and assessments

Time point	Visit −1	Visit 0 OR	Visit 1 Day 1–6	Visit 2 Day 7	Visit 3 Discharge	Visit 4 6 months	Visit 5 12 months	Visit 6 18 months	Visit 7 24 months
Day/month		d0		d7		m6	m12	m18	m24
Visit window									
**Eligibility screens**									
**Demographic data**									
Gender	x								
Year of birth	x								
Body height	x								
Body weight	x								
Inclusion and exclusion criteria	x								
**Informed consent**	x								
**Allocation/randomization**		x							
**Intervention**									
Liver biopsy at the end of LT and after 6 months		x				x			
**Baseline variables**									
**Donor/recipient#**	x								
Transplant listing timepoint	x								
**Underlying liver disease** (Hep C, Hep B, Hep A, Hep E, NASH, ASH, PSC, PBC, autoimmune)	x								
**Donor information**									
BMI	x								
Donor risk index	x								
Cold ischemia time		x							
Preservation solution		x							
**Machine perfusion**									
Machine perfusion time		x							
Machine perfusion type		x							
Machine perfusion pressure		x							
Machine perfusion oxygenation		x							
Asservation of 10 ml machine perfusate		x							
**Blood values**									
ALT		x	x	x	x				x
AST		x	x	x	x				x
INR		x	x	x	x				x
Bilirubin		x	x	x	x				x
Alkaline phosphatase		x	x	x	x				x
**HMBG-1 in blood***		x		x					
**Circulating tumor DNA***		x			x	x			
MELD score		x							
Creatinine		x		x					x
Serum alpha-fetoprotein		x				x	x	x	x
**Intraoperative course**									
Number of RBC units during OLT		x							
Duration of OLT		x							
Type of OLT		x							
**Postoperative course**									
PNF				x					
EAD				x					
HAT				x	x	x	x	x	x
ICU stay					x				
Hospital stay					x				
Type of immunosuppressive therapy					x				
Tacrolimus level				x	x	x	x	x	x
Rejection Activity Index (RAI)						x			
**Tumor criteria in explanted liver**									
RNA sequencing				x					
Phenotyping				x					
Follow-up									
CT (abdominal and thoracic)						x	x	x	x
Number of liver-related complications			x	x	x	x	x	x	x
Clavien grading			x	x	x	x	x	x	x
Adverse events/safety	x	x	x	x	x	x	x	x	x

^#^Donor age, donor BMI, donor cause of death (CVI, trauma, hypoxia, cardiac arrest, other), recipient MELD score, INR, bilirubin, creatinine at transplant, balance of risk (BAR) score), AST, ALT before transplant

^*^Parameters with * have to be centrifugated within 4 h and stored at −80 °C until centralized analysis

### Sample size {14}

The sample size was calculated to show superiority of HOPE over conventional cold storage regarding HCC recurrence-free survival (time to HCC recurrence or death). The power was set to 80% at a significance level of 5%. Based on previous studies on Liver transplantation in patients with HCC, we expect that 15% of the patients in the control arm will develop tumor recurrence or die within 24 months [2, 26–28]. Based approximately on the results of a retrospective cohort study, we expect this risk to be reduced to 5% of the patients in the HOPE arm [14]. Under the assumption of exponential survival times, these rates correspond to a hazard ratio (HR) of 0.32. We expect an accrual period of 12 months and plan a minimum follow-up duration of 24 months (resulting in a total study duration of 36 months). Based on the method of Lachin and Foulkes and as implemented in the function *nSurvival* from the R package *gsDesign*, we will need 208 patients to be able to observe 26 events [29–31]. We expect a dropout rate of 5%, similar to the dropout rate of 4% observed in Schlegel et al. [18]. We will thus need to recruit 220 patients (110 per treatment arm).

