## Statistical methods

### Statistical methods for analyzing primary and secondary outcomes {20a}

Detailed methodology for summaries and statistical analyses of the data collected in the trial will be documented in a separate statistical analysis plan. The statistical analysis plan will be finalized before database closure and will be under version control at the Department of Biostatistics, University of Zurich.

We will estimate the hazard ratio (HR) for the effect of HOPE versus conventional cold storage on the primary outcome and report the HR with a 95% confidence interval (CI) and a *p* value for the test of the null hypothesis of a HR of 1. To account for variability between centers, we will use a mixed-effects Cox model with treatment as a fixed factor and a random intercept per center, as implemented in the R package coxme, i.e., a frailty model with Gaussian frailty distribution [33]. The advantage of a mixed-effects Cox model over other approaches to account for between-center variability with time-to-event outcomes (e.g., center as fixed effect or stratification for center in standard Cox models) is that small numbers of patients and events per center are better handled [34]. It should be noted that the estimated HR will compare the hazard rates of two subjects, one treated with HOPE and one with conventional cold storage, randomly drawn from the same center (conditional HR, center-specific interpretation). We will assess the proportional hazards assumption by inspecting the scaled Schoenfeld residuals. HCC recurrence-free survival in the two trial arms will be graphically displayed by Kaplan–Meier curves. The analysis will be performed on the FAS (see item 20c). Patients who are lost to follow-up or withdraw from the trial will be right censored at their last follow-up visit.

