### Interim analyses {21b}

When 165 patients are recruited (75% of 220 patients), a blinded sample size re-estimation will be performed. We will use the method proposed by Todd et al. for designs with flexible follow-up [38]. We will compare the average survival probability over both trial arms, S_new_(t), at t = 6, 12, 18, and 24 months of follow-up, from the data ad interim with the anticipated survival probability used for the original sample size estimation, S_orig_(t). The average difference (on the complementary log-log scale) will then be used to predict the overall tumor recurrence-free survival probability at 24 months, S_new_(24). We will re-estimate the required number of patients for the trial not only accounting for changes in survival probabilities but also for changes in the recruitment rate or in the dropout rate. The sample size will be increased if S_new_(t) > S_orig_(t) on average, i.e., if fewer events than expected are observed, given that the recruitment rate is as expected. A reduction of the sample size will not be considered. There are no statistical rules for stopping the trial earlier, neither for efficacy nor for futility.

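### The 5% HOPE-arm risk of recurrence or death is taken from a recurrence-only result, so the stated 80% power rests on unstated conditions about deaths without recurrence

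*Protocol article*

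**What the plan says.** Outcomes {12} defines the primary endpoint as "the time interval until either tumor recurrence is observed or the patient dies from any cause". Death from causes other than HCC is also listed there as a separate component.

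Sample size {14} states "we expect that 15% of the patients in the control arm will develop tumor recurrence or die within 24 months", and then, relying approximately on one retrospective cohort, "we expect this risk to be reduced to 5% of the patients in the HOPE arm". With exponential times this becomes a hazard ratio of 0.32. Of the error rates it says "The power was set to 80% at a significance level of 5"%. The result is 208 patients and 26 events, or 220 patients after 5% dropout.

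Background and rationale {6a} describes that same cohort as showing "a significant reduction of tumor recurrence rate from 25.7% in un-perfused donation after brain death (DBD) Livers compared to only 5.7"% in recipients of HOPE-treated DCD livers. Eligibility criteria {10} excludes DCD grafts. The Background also quotes "overall 5-year survival rates of 70"% after liver transplantation.

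Interim analyses {21b} plans a blinded re-estimation: "The sample size will be increased if S_new_(t) > S_orig_(t) on average". A reduction is ruled out.

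**The concern.** A recurrence result has been used as the risk for a composite that also counts every death. The assumed composite of 5% is even slightly below the recurrence-only 5.7% of its source. Whatever the true risk of death without recurrence, the HOPE arm has no allowance for it.

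If HOPE acts on the tumour and leaves other deaths unchanged, those deaths occur at the same rate in both arms and pull the hazard ratio for recurrence-free survival towards 1. Power then falls below the stated 80%. At stake is how a non-significant result would be read: it could be taken as absence of an anti-cancer effect when the endpoint had been diluted by other deaths.

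**Working it through.** **1. Reproducing the plan.** Inputs from Sample size {14}: 24-month risks of 15% and 5%, 12 months' accrual, 36 months in total, 1:1 allocation. The section does not state sidedness. Two-sided 5% reproduces the stated size, whereas one-sided 5% would give 165 patients.

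- Hazards, λ = −ln(1−p)/24: control 0.00677, HOPE 0.00214, mean 0.00445 per month. HR = ln 0.95 / ln 0.85 = 0.316.
- Event probability with uniform accrual, P(λ) = 1 − [exp(−24λ) − exp(−36λ)]/(12λ): 0.1836, 0.0621, and 0.1250 at the mean hazard.
- Lachin–Foulkes on the log-hazard scale: N = {[1.960·√(4/0.1250) + 0.842·√(2/0.1836 + 2/0.0621)] / ln 0.316}² = 207.5, so 208.
- Events = 207.5/2 × (0.1836 + 0.0621) = 25.5, so 26. Power at 208 is 80.1%.

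The arithmetic is right. Only the 5% input is in question.

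**2. The 5% beside the protocol's survival figure.** With a constant hazard (an approximation), 70% five-year survival means 1 − 0.70^(24/60) = 13.3% deaths from all causes by 24 months. A 5% composite caps all-cause death at 5% and extrapolates to 0.95^2.5 = 88% five-year recurrence-free survival, against 70% overall survival. The control 15% extrapolates to 0.85^2.5 = 67%, which is compatible with 70%.

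**3. Range for non-HCC death, d.** The protocol gives no 24-month figure, so d is assumed. For orientation only: if 15% recur and every recurrence is fatal within five years, 30% − 15% = 15% die without recurrence by five years, which is 1 − 0.85^0.4 = 6.3% at 24 months. With 20% recurrence, the upper figure in the Discussion, it is 1 − 0.90^0.4 = 4.1%. Both treat undated recurrence figures as five-year figures. A range of 2% to 8% is used below.

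**4. Power at 208 patients, d equal in both arms.** Let λd = −ln(1−d)/24. Two choices are open.

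- Control arm: either 15% is the recurrence risk and d is added to it, or 15% is the composite as stated and d lies inside it.
- Effect on recurrence: the planned HR of 0.316, or the cohort's own, ln(1−0.057)/ln(1−0.257) = 0.198.

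Example, d = 5% (λd = 0.00214). Added on top with HR 0.316: control 0.00677 + 0.00214 = 0.00891, HOPE 0.00214 + 0.00214 = 0.00427, composite HR 0.48. Inside the 15%: control recurrence hazard 0.00677 − 0.00214 = 0.00463, HOPE 0.316 × 0.00463 + 0.00214 = 0.00360, composite HR 0.53.

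| Control arm | Recurrence HR | d at 24 months | Composite HR | Power |
|---|---|---|---|---|
| 15% recurrence, plus d | 0.32 | 3 / 5 / 8% | 0.42 / 0.48 / 0.55 | 68 / 60 / 51% |
| 15% composite, including d | 0.32 | 2 / 3 / 5% | 0.40 / 0.44 / 0.53 | 66 / 57 / 41% |
| 15% composite, including d | 0.20 | 2 / 3 / 5% | 0.30 / 0.35 / 0.45 | 83 / 75 / 56% |
| 15% recurrence, plus d | 0.20 | 3 / 5 / 8% | 0.32 / 0.39 / 0.47 | 84 / 78 / 68% |

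Log-rank simulations of the first three rows mostly agreed within 3 points and were at most about 4.5 points lower.

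**5. The blinded review.** Planned pooled 24-month recurrence-free survival is (0.85 + 0.95)/2 = 0.90. In every cell above with power below 80%, the pooled value is under 0.90, for example 0.83 in the first row at d = 8% and 0.89 in the second at d = 3%. On survival grounds the rule then triggers no increase.

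**The case against.** The calculation is correct, so this disputes an assumption. The protocol says that the 5% is only approximately based on the cohort, and its HR of 0.32 is weaker than the 0.20 that the cohort's rates imply. A reader might infer that 0.32 is simply a recurrence hazard ratio relabelled. The protocol does not show that, and 0.32 could be read as an already diluted value: the last table row gives exactly 0.32 at d = 3%. This stands, and it is why the range includes 0.20. But the protocol does not give that derivation. The cohort is retrospective, compared different graft types, and its follow-up time is not given here. For the same reason, 5% lying below 5.7% is a warning sign and not proof of an impossible assumption.

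A reader might also infer that the control 15% omits deaths because it equals the recurrence figure in the Background. The protocol states it as a composite with its own references, the recurrence figures there carry no time horizon, and 15% fits 70% five-year survival. It is not shown to be wrong.

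Nor does the survival figure strictly contradict the 5%. It is a background five-year figure, its conversion to 24 months needs a constant hazard, and the 13.3% includes HCC deaths. The Background also says that machine perfusion improves graft survival, so some effect on other deaths is plausible. Nothing in the protocol, however, supports an effect on them as large as that on recurrence.

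Finally, a reader might call the re-estimation rule defective. Any blinded method based on pooled rates corrects the event rate and not the treatment effect, so this is a limit of the method. The components are analysed separately at the end, so dilution would be visible then, though not at the interim review.

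**Conclusion.** The point holds as an under-justified input that makes the stated power conditional, and it should be fixed. The 80% holds only if HOPE lowers non-HCC death about as much as recurrence, if its effect on recurrence is clearly stronger than HR 0.32, or if non-HCC death is very rare. With HR 0.32 on recurrence and equal non-HCC death, power is about 41% to 68% over the values tabulated. With HR 0.20 it is about 56% to 84%, and stays at or above 80% only for d of about 2% (control composite held at 15%) to about 4% (d added to it).

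These figures rest on exponential times, a two-sided 5% test, equal non-HCC death in both arms and an assumed d. No single power figure, and no narrow band, follows from the documents.

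**What to change.** In Sample size {14}, state the assumption by component: 24-month recurrence and 24-month death without recurrence, per arm, each with its source. Give the power of 208 evaluable (220 recruited) patients as a range over the non-HCC death risk and the recurrence hazard ratio, and state in one sentence the conditions under which 80% holds. If 0.32 was meant as a cohort effect already weakened for other deaths, say so and show the step.

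In Interim analyses {21b}, add that the blinded review also reports pooled counts of recurrences and of deaths without recurrence. Pooled counts keep the blind and make dilution visible where the survival-based rule would stay silent.

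The cost is a rewritten paragraph, one added line and a less favourable stated power. No additional patients, visits or data are requested.

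### The 26 events and 80% power assume every event is seen up to month 36, but recurrence is looked for only by 6-monthly CT, with no settled schedule after month 24

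*Protocol article*

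**What the plan says.** Sample size {14} of the protocol article sets power at 80% and significance at 5%. For control, "we expect that 15% of the patients in the control arm will develop tumor recurrence or die within 24 months"; for the intervention, "we expect this risk to be reduced to 5% of the patients in the HOPE arm". With exponential times, "these rates correspond to a hazard ratio (HR) of 0.32". On timing, "We expect an accrual period of 12 months and plan a minimum follow-up duration of 24 months", which makes 36 months in total. By the Lachin–Foulkes method, "we will need 208 patients to be able to observe 26 events". Allowing 5% dropout, 220 are recruited.

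Outcomes {12} defines the endpoint as recurrence or death from any cause. It states that "HCC recurrence is assessed by computed tomography (CT) at 6, 12, 18, and 24 months", then 6-monthly where appropriate until the study ends. Table 1 has no visit after month 24, and its CT row stops there.

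The primary analysis in {20a} is a Cox model with "a random intercept per center, as implemented in the R package coxme". It does not say whether the p value comes from a Wald, score or likelihood-ratio test. Interval censoring is handled in a Weibull sensitivity analysis. The blinded re-estimation in {21b} compares pooled survival at 6, 12, 18 and 24 months.

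**The concern.** The sample size calculation and the assessment schedule describe different observation schemes. The calculation lets a patient followed for 24 to 36 months contribute an event at any moment up to closure. Under the written schedule, a recurrence arising after a patient's last CT does not show up at any scheduled assessment. The calculation takes a noticeable part of its events from exactly that window.

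At about 26 events, losing two or three matters. The trial would be run and interpreted as having 80% power when the written schedule delivers less. The re-estimation is unlikely to reveal this. It looks only at months 6 to 24, and if the events are recurrences, survival at those visits is the same under CT assessment as under continuous observation.

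**Working it through.** **Inputs.** From Sample size {14}: 24-month risks of 15% and 5%, 12 months' accrual, 36 months in total, 208 patients before and 220 after 5% dropout. From Outcomes {12} and Table 1: the CT schedule. Assumed: two-sided 5% (which reproduces the stated N; one-sided does not), uniform accrual, and the share of events that are deaths (0–50%, since the article gives none).

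**1. Reproducing the plan.**
- Hazards per month: −ln(0.85)/24 = 0.006772 and −ln(0.95)/24 = 0.002137. HR = 0.3156, stated as 0.32.
- Probability of an event by closure: E(λ) = 1 − [exp(−24λ) − exp(−36λ)]/(12λ). This gives 0.1836 (control), 0.0621 (HOPE) and 0.1250 at the mean hazard.
- N = [1.96·√(4/0.1250) + 0.8416·√(2/0.1836 + 2/0.0621)]² / (ln 0.3156)² = (11.09 + 5.53)²/1.330 ≈ 207.5, so 208.
- Events: 207.5/2 × (0.1836 + 0.0621) ≈ 25.5, so 26.
- 208/0.95 = 218.9, so 219, or 220 for equal arms.

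All stated figures reproduce.

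**2. Events that depend on follow-up after month 24.** By month 24, 208 patients yield 104 × (0.15 + 0.05) = 20.8 events. The remaining 25.5 − 20.8 = 4.7, about 5, arise between months 24 and 36.

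**3. Events seen on the CT grid, by hand (208 patients, no dropout, all events recurrences).** With uniform accrual, half the patients have under 30 months of follow-up and a last CT at month 24. The other half have a last CT at month 30.
- Month-30 risks: 1 − 0.85^1.25 = 0.1838 and 1 − 0.95^1.25 = 0.0621.
- Average probability of a detected event: (0.15 + 0.1838)/2 = 0.1669 and (0.05 + 0.0621)/2 = 0.0561.
- Events: 104 × (0.1669 + 0.0561) ≈ 23.2.

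**4. Power by simulation.** 220 recruited, 5% dropout, Cox model with treatment only and Efron ties. Recurrence is dated at the next CT and deaths exactly.

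| Recurrence assessment | Deaths among events (assumed) | Observed events | Power: Wald / score / likelihood ratio |
|---|---|---|---|
| Exact times to closure | – | 26.3 | 77.3 / 79.3 / 79.9% |
| 6-monthly CT continues | 0% | 23.8 | 72.9 / 75.3 / 76.1% |
| 6-monthly CT continues | 30% | 24.6 | 74.3 / 76.6 / 77.2% |
| 6-monthly CT continues | 50% | 25.1 | 75.4 / 77.6 / 78.2% |
| CT stops at month 24 | 0% | 21.5 | 66.6 / 70.3 / 71.4% |
| CT stops at month 24 | 30% | 23.0 | 70.1 / 72.8 / 73.8% |
| CT stops at month 24 | up to 50% | up to 23.8 | up to 76% |
| 6-monthly CT plus CT at closure | 0–50% | about 26 | about 77–80% |

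Monte Carlo error is up to about 1 point. Centre variance is not given and was not simulated.

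**5. The part due to CT.** With the likelihood-ratio test held fixed, continuing 6-monthly CT costs 79.9 − 76.1 = 3.8 points with no deaths and 79.9 − 78.2 = 1.7 points with 50% deaths. Stopping CT at month 24 costs 79.9 − 71.4 = 8.5 points with no deaths and 79.9 − 73.8 = 6.1 points with 30% deaths.

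**The case against.** The strongest defence is that nothing in the sample size section is miscalculated. A reader might infer an arithmetic error; there is none, as step 1 shows.

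A reader might also infer that the design cannot reach its figures in any circumstances. That is not supported either. Recruitment is 220, not 208, and dropouts contribute until they are censored. With exact times or a CT at closure, 220 patients give about 26 events and about 80% by likelihood ratio. The article neither provides for nor excludes a closing CT.

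Deaths are not tied to CT and their share is unstated, so no single event count follows from the article. Recurrences might also be found outside scheduled CT, because {18a} collects histology and radiology reports and {18b} provides oncologic follow-up. That would narrow the gap by an amount the article does not let one calculate.

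It is tempting to count the Wald test's 2–4 point loss against likelihood ratio as a fault. The article does not name Wald, and the form of the test belongs in the separate statistical analysis plan. It explains part of the width of the ranges and is not part of the error.

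Two other defences do not remove the point. The Weibull sensitivity analysis models interval censoring but cannot restore events that no CT detected. The re-estimation compares survival only up to month 24, so it does not target a loss after that.

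**Conclusion.** The point stands as a mismatch between the observation assumed in the sample size and the observation scheduled. The figures of 208, 26 and 80% are right for continuous observation to month 36. For 220 recruited with 5% dropout, expect about 24–25 events and 72–78% power if 6-monthly CT continues, and about 21–24 events and 66–76% if it ends at month 24 as Table 1 shows. A CT at closure brings this to about 26 events and 77–80%.

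These ranges rest on the protocol's own risks and accrual, a 0–50% share of deaths, any of the three standard Cox tests, no detection outside scheduled CT, and no centre variance. The loss is modest if CT continues and larger if it does not. Which case applies cannot be read from the article.

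**What to change.** Reconcile Outcomes {12}, Table 1 and Sample size {14} on how recurrence is assessed between month 24 and study closure, including whether any CT is done at closure. Which schedule to adopt is for the sponsor. Then restate in {14} the expected observed events and power under that schedule, with the assumed share of deaths. Use those figures as the starting point for the blinded re-estimation in {21b}.

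Moving the data cut does not solve this. With 12 months of staggered accrual, one calendar date cannot coincide with every patient's last CT, and cutting each patient at the last CT adds no recurrences.

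The cost is a change of wording and a slightly less favourable stated power. No extra patients are needed. Restating the power discloses the loss and does not restore 80%. For scale, if all events are recurrences on a continuing 6-monthly grid, about 250 recruited would give 79–81%.
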